### 2.9. Sample Size and Power

Through convenience sampling, a subsample of residents from three countries (the Netherlands, Germany, and Norway) from the MIDDEL trial was asked to participate in this substudy. The aim was to include 50 care home residents in every group (GMT, RCS, GMT plus RCS, control group at baseline). The Netherlands and Germany aimed to include 8 CHUs/80 participants each, and Norway aimed to include 4 CHUs/40 residents. Attrition of residents was expected to occur due to mortality, moving to another care home, or refraining from participation in the substudy. The mean length of stay in a care home in the Netherlands is 8 to 12 months. A mortality rate of 20% within the intervention period of 6 months (primary outcome at 6 months) was taken into account with respect to the sample size. Mortality is lower in care home residents with mild to moderately severe dementia (compared to severe and very severe). The power for this exploratory substudy with this given sample size was difficult to determine because there are no previous studies or agreed minimal clinically important difference for this combination of intervention, population, and outcome. As in the MIDDEL protocol [1], the main effects in this substudy were tested as GMT versus no GMT and RCS versus no RCS so that all participants with available data could be used in each test. Thus, after a dropout of 20% until the primary endpoint of 6 months, as assumed in the MIDDEL protocol, we expected to have 160 participants in total. Compared to the MADRS, we expected the cluster effect in these biological indicators to be smaller, with an ICC ≤ 0.01. The average cluster size after 20% dropout will be eight. Because there are two main comparisons, tests were Bonferroni-corrected from 5% to 2.5%, two-sided. We used R to determine the effect size for which 80% power is reached with a two-sample *t*-test with 160 participants in total, adjusted for clustering, with a two-sided 2.5% significance level, and found that the effect size that can be reliably determined with this substudy is d = 0.51, i.e., a medium effect size [51]. This seems reasonable compared to previous studies of music therapy [14,52]. The actual power may be higher in a longitudinal model if time points are correlated.

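### The two main comparisons use single-step Bonferroni; Holm's step-down keeps the same 5% family-wise error, is never less powerful and takes one sentence (a cheap improvement, not an error)

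*Protocol article*

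**What the plan says.** All of this stands in Section 2.9 (Sample Size and Power) of the protocol article. The substudy uses the factorial margins of the parent trial: "the main effects in this substudy were tested as GMT versus no GMT and RCS versus no RCS". On multiplicity it says: "Because there are two main comparisons, tests were Bonferroni-corrected from 5% to 2.5%, two-sided". The power calculation uses the same level, "with a two-sided 2.5% significance level", and arrives at a detectable d of 0.51.

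The multiplicity sentence describes how the tests are done, not only how the sample was sized. Sections 2.10 and 2.11 do not restate or change it. No step-down, hierarchical or alpha-recycling rule appears anywhere in the article, so each comparison stays at 2.5% whatever the other one shows.

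**The concern.** Bonferroni and Holm both control family-wise error strongly at 5%, without any assumption on the dependence between the tests. Holm tests the smaller p-value at 2.5% and, if that is significant, the larger at 5%. It therefore rejects whatever Bonferroni rejects, and also the second comparison when its p-value lies between 2.5% and 5% and the first has succeeded. On the same two p-values, single-step Bonferroni is the dominated choice.

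At stake is power for the second comparison. The Introduction sets out to compare RCS, GMT and their combination with usual care, so conclusions on both interventions are of interest. By its own calculation the substudy can reliably detect only a medium effect.

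**Working it through.** **Inputs (Section 2.9)**
- Residents analysed at 6 months: "we expected to have 160 participants in total".
- Allocation: "The aim was to include 50 care home residents in every group", four arms, so each factorial margin is 1:1, about 80 against 80.
- Clustering: "with an ICC ≤ 0.01" and "The average cluster size after 20% dropout will be eight".
- Power target: "We used R to determine the effect size for which 80% power is reached".
- Level: two-sided 2.5% per comparison.

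**Reproducing d = 0.51**
- Design effect = 1 + (8 − 1) × 0.01 = 1.07.
- Effective N = 160 / 1.07 = 149.5, or 74.8 per side.
- The noncentral t, two-sample test at two-sided 2.5%, gives 80% power at d = 0.509. The stated 0.51 is reproduced.
- At two-sided 5% the same calculation gives d = 0.461. This is the level that applies to the second comparison under Holm once the first has been rejected.

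**Power formulas**

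Let a be the power of a comparison at 2.5%, b its power at 5%, and g = b − a. In a balanced 2×2 layout the two main-effect contrasts are orthogonal, so the two tests are taken as independent.
- Comparison 1 under Bonferroni: a₁. Under Holm: a₁ + g₁ × a₂.
- Both under Bonferroni: a₁ × a₂. Under Holm: a₁ × a₂ + a₁ × g₂ + a₂ × g₁.
- At least one, under either method: 1 − (1 − a₁)(1 − a₂), because the first step is identical.

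**Both effects 0.51:** a = 0.802, b = 0.872, g = 0.070.
- Each: 0.802 → 0.802 + 0.070 × 0.802 = 0.859 (rounded from unrounded inputs).
- Both: 0.802² = 0.644 → 0.644 + 2 × 0.802 × 0.070 = 0.756.

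**Other scenarios.** At d = 0.30, a = 0.336 and b = 0.445. For a true null, a = 0.025 and b = 0.05. In each cell the first figure is Bonferroni and the second Holm.

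| True effects | First comparison | Second comparison | Both rejected | At least one (either method) |
|---|---|---|---|---|
| 0.51 and 0.51 | 80.2% → 85.9% | 80.2% → 85.9% | 64.4% → 75.6% | 96.1% |
| 0.51 and 0.30 | 80.2% → 82.6% | 33.6% → 42.4% | 27.0% → 38.1% | 86.9% |
| 0.30 and 0.30 | 33.6% → 37.3% | 33.6% → 37.3% | 11.3% → 18.6% | 56.0% |
| 0.51 and 0 | 80.2% → 80.4% | 2.5% → 4.5% (false rejection) | 2.0% → 4.2% | 80.7% |

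**Family-wise error.** With both effects null it is 1 − 0.975² = 4.94% under either method. With one true effect of 0.51 and one null it is 4.5% under Holm, below 5%.

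**Sensitivity**
- With normal test statistics, power to show both effects of 0.51 goes from 65.6% to 76.4% at correlation 0 and from 70.0% to 78.9% at correlation 0.5.
- In a unit-level simulation (20 units of 8, ICC 0.01, 17 degrees of freedom), each comparison goes from about 74% to 80% and both from about 57% to 70%. Absolute power is lower there, but the gain is similar.

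**The case against.** The strongest objection is that nothing here is wrong. Bonferroni is valid, d = 0.51 reproduces, and a simple correction is a defensible choice in a substudy that calls itself exploratory. That stands as far as it goes: this is a gain in efficiency and not a defect. It does not remove the point, because the plan itself chose formal family-wise control and a better procedure gives the same control. An unseen analysis plan might say otherwise, but the article states its choice explicitly.

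Four further objections limit the size of the point.
- **The 64% to 76% figure needs both effects to be 0.51.** Section 2.9 says that no earlier studies exist for this combination of intervention, population and outcome. If only one factor works, its power hardly moves. This stands.
- **No section makes significance on both factors a success criterion.** Two significant margins also do not test a difference between GMT and RCS. This stands: the gain is useful but not required by the stated aim.
- **The change is not wholly free.** Bonferroni decisions match 97.5% intervals; Holm decisions need not. This stands as a small cost.
- **The family is not settled.** Sections 2.6.1, 2.6.2 and 2.10.1 name two co-primary parameters, hair cortisol and PSS-10, modelled at 3 and 6 months. If Holm is applied to each parameter separately, with one effect of 0.51 and one null in each and the outcomes independent, the chance of any false rejection rises from 1 − 0.975² = 4.9% to 1 − 0.9549² = 8.8%. This stands, and is why the fix must name the family.

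A reader might infer that the plan fails to control error for its two comparisons, that d = 0.51 is miscalculated, or that Holm would raise the chance of a positive result overall. The documents and the arithmetic support none of these.

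**Conclusion.** This is a cheap improvement, not an error. For the two main comparisons, Holm's procedure keeps the 5% family-wise error that Section 2.9 aims for and is never less powerful than the fixed 2.5% level.

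At the plan's own detectable effect in both factors, the gain is about 6 percentage points per comparison and 11 for showing both. With both effects at 0.30 it is about 4 and 7 points. It is close to nil for the true effect if only one factor works, and always zero for the chance of at least one significant result.

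These figures assume equal arms, 160 residents analysed, a design effect of 1.07 and uncorrelated test statistics. The dominance of Holm over Bonferroni needs none of these assumptions.

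**What to change.** In Section 2.9, replace the Bonferroni sentence by text such as: *The GMT and RCS main-effect tests for [named outcome and time point] are done with Holm's step-down procedure at a family-wise two-sided 5% level: the smaller p-value is tested at 2.5% and, if it is significant, the larger at 5%.*

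- **Family.** Name the outcome and time point whose two p-values form it. If it is widened to both co-primary parameters, apply Holm across all tests in the family and not within each parameter. With four tests the first threshold is 5% / 4 = 1.25%.
- **Planning value.** For the two-test family keep d = 0.51. It is the detectable effect at the first-step level and so is conservative. A wider family would need it recalculated, because it rests on 2.5%.
- **Intervals.** If 97.5% intervals are reported, state that they are not matched to the Holm decision. When the second p-value lies between 2.5% and 5%, the interval includes zero although Holm rejects.

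The cost is one sentence and no extra residents. The Data Availability section says that data are still to be collected, so the change can be prespecified if it is made before the analysis.

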### 2.10. Data Analysis

#### 2.10.1. Co-Primary Study Parameters

Stress (HC concentrations and perceived stress measured with the PSS-10) after 3 and 6 months was modeled to account for differences in therapy (RCS compared to no RCS, GMT compared to no GMT, additional effects of GMT + RCS combined, and baseline differences in stress (HC concentrations and perceived stress measured with the PSS-10) (T0).

#### 2.10.2. Secondary Study Parameters

In the final model in which MADRS scores at the endpoints (3 and 6 months) are predicted by the therapy group (Gold et al., 2019), baseline stress was added to examine whether chronic stress (HC concentrations; perceived stress) predicts the treatment effect. Secondary study parameters were added to the final model. A description of the effect of amylase response (expected to change at 15 min), cortisol response (expected to change at 60 min), and experienced stress (assessed with the VAS) were provided. Correlation of stress biomarker response (SC and SAA levels at T3 and T6, pre-post treatment) and change in MADRS score (T3–T0 and T6–T0) were examined. The design was able to account for between-group variation (including differential responses in three groups) and within-group variation (changes in participants between 3 months, 6 months, and baseline).

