## Abstract

Recently, a large cluster-randomized controlled trial was designed—Music Interventions for Dementia and Depression in ELderly care (MIDDEL)—to assess the effectiveness of music interventions on depression in care home residents with dementia (ClinicalTrials.gov NCT03496675). To understand the pathophysiological mechanisms, we observed the effect of repeated music interventions on stress in this population since chronic stress was associated with depression and an increased risk for dementia. An exploratory study was designed to assess: (1) changes in hair cortisol concentrations as an indicator of longer-term stress; (2) whether baseline stress is a predictor of therapy outcome; (3) pre- and post-treatment effects on salivary α-amylase and cortisol response as an indicator of immediate stress in 180–200 care home residents with dementia and depressive symptoms who partake in the MIDDEL trial. Insights into mediatory effects of stress to explain the effect of music interventions will be gained. Hair cortisol concentrations were assessed at baseline and at 3, 6, and 12 months along with the Perceived Stress Scale. Salivary α-amylase and cortisol concentrations were assessed at 1, 3, and 6 months. Saliva was collected just before a session and 15 and 60 min after a session, along with a stress Visual Analogue Scale.

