#### 2.6.3. Secondary Study Parameters: Salivary Cortisol and Alpha-Amylase

SC can provide more insight into how well the endocrine stress system responds to an immediate intervention because HC does not provide insight into how well the HPA axis functions. As residents with depressive symptoms were expected to have steeper cortisol slopes, we hypothesized that participants have a higher SC before the start of the music session, and participating in the music intervention attenuates the SC. Samples were collected on days a music or book reading session took place, between 12.00 and 17.00 h, preferably at 15.00 h, to minimize any confounding effects of the diurnal hormonal rhythm. In order to assess the immediate effects of music interventions on stress, saliva samples were collected to assess SC and SAA levels just before, 15 min after, and 60 min after the music/book reading session. Multiple measurements of SC and SAA per resident were required because of variations in levels over time within residents [15]. The assessment took place at T1 (within 1 month after the music interventions started or within 1 month after completion of the baseline assessment in the control group), T3 (3 months), and T6 (6 months). The days were selected according to logistic convenience (the first session that took around 15.00 h around T1, T3, and T6 were selected).

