#### 2.6.4. Secondary Study Parameters: Proxy- or Self-Reported Experienced Stress

On days when saliva samples are collected, residents or a proxy reported any experienced stress using a Stress Visual Analogue Scale (VAS). The VAS is a vertical line of 100 mm with endpoints labeled ‘The least stress you can imagine’ (0) and ‘The most stress you can imagine’ (100). Residents or their proxies were asked to indicate on this line how stressed they felt at that exact moment. The scale thereby provides a single score between 0 and 100, representing subjective stress [36]. The VAS was filled out at T1, T3, and T6. Similar to the collection of saliva samples, the VAS was filled out—by proxy if necessary—just before, 15 min, and 60 min after the music or book reading session.

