### 2.7. Data Collection Procedures

Biomarkers were collected throughout the trial to assess the immediate and longer-term effects of repeated music interventions on chronic and immediate stress in care home residents with dementia and depressive symptoms (Figure 2). In Figure 2, the stress assessments of the substudy are presented within the assessment schedule of the MIDDEL trial. Hair samples were collected in all groups at T0, T3, T6, and T12 to assess physiological changes in chronic stress. Saliva samples were collected in the RCS, the GMT, and the control group at T1, T3, and T6. Saliva samples were collected just before, 15 min, and 1 h after the intervention to assess the immediate intervention effects. The group GMT plus RCS were only included to assess the longer-term effect of repeated music intervention on (chronic) stress.

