### 2.11. Statistical Analyses

Data were analyzed using SPSS Statistics version 26. Immediate and chronic stress were assessed with psychological subjective indicators of stress and physiological markers of stress. Descriptive statistics (mean, standard deviation, range) were calculated for demographics, the PSS, and VAS scores for all time points. Power calculations were computed. In addition, we reported effect size estimates. The distribution was assessed, and if needed, data were log-transformed to be normally distributed accordingly, especially since cortisol and SAA data may have a positively skewed distribution.

The effect of repeated music interventions on chronic stress was measured with the biomarker HC. HC concentrations were reported in pg/mg. Concentrations of HC at baseline were assessed as a predictor of treatment response. In order to assess the association between the HC concentration and perceived stress (PSS-10), correlations were computed. Changes in HC concentrations over time and perceived stress (PSS-10) were assessed. The levels of stress after 3 and 6 months were modeled to account for differences in therapy: RCS compared to control (usual care or book reading), GMT to control, GMT + RCS, and baseline differences in stress (T0). In the final model, in which MADRS scores at the endpoints (3 and 6 months) were predicted by the therapy group, baseline stress was added to observe whether there was a change in treatment effect. The analyses included a correlation between stress reduction (at T3, pre-post treatment) and change in MADRS score (T6–T3–T0).

SC and SAA were concomitantly measured and were used as outcome measures to assess whether changes in activity in the HPA axis and the ANS axis occurred pre- and post-intervention. Pre- and post-sampling weight of saliva samples were measured. Levels of SC were reported in nmol/L and levels of SAA in U/mL. Adherence to instructions prior to the collection of the saliva sample was assessed. A description of the effect of SAA response (expected to change at 15 min) and SC response (expected to change at 60 min) was provided. The design is able to account for between-group variation (including differential responses in four groups) and within-group variation (changes in participants between 3months, 6 months, and baseline). Exploratory subgroup analyses and moderator analyses were performed.

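### Adding the saliva and session-VAS measures to the MADRS therapy model removes the GMT + RCS arm, and its therapy coefficient is no longer the total effect to the extent that therapy changes those measures

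*Protocol article*

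**What the plan says.** Section 2.10.2 builds on the main trial's depression model: "In the final model in which MADRS scores at the endpoints (3 and 6 months) are predicted by the therapy group". Baseline chronic stress (hair cortisol and perceived stress) is added to it, and then comes the sentence at issue: "Secondary study parameters were added to the final model".

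The outcome sections define which variables these are. Section 2.6.3 is headed "Secondary Study Parameters: Salivary Cortisol and Alpha-Amylase", and Section 2.6.4 gives the stress VAS under the same label and ties it to the days of saliva collection.

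On timing and arms, Section 2.7 says: "Saliva samples were collected in the RCS, the GMT, and the control group at T1, T3, and T6". It keeps the combined arm for the longer-term question only, and the Figure 1 legend confirms that no saliva was taken there. Section 2.3 places randomisation after the baseline assessments. Section 2.6.3 places T1 after the music interventions have started, and hypothesises that the music session lowers salivary cortisol.

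Section 2.11 describes the MADRS model again, this time with baseline stress as the only addition, and treats salivary cortisol and α-amylase as outcomes. The saliva paragraph there ends with a statement about the design, "including differential responses in four groups"; the matching statement in Section 2.10.2 gives three groups.

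**The concern.** A covariate in a model that estimates a randomised therapy effect should be fixed before treatment and available in every arm. These measures are neither.

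- **Arm coverage.** The combined arm has no values at all. Fitted to complete cases, the model becomes a three-arm model, and the additional effect of GMT + RCS, which Section 2.10.1 sets out to model for stress, has no data for MADRS. Imputation has no observed value in that arm to draw on. Residents with swallowing difficulties, or judged unable to follow the procedure, also lack saliva (Section 2.2).
- **Timing.** The markers are measured under treatment and are expected to respond to it. Conditioning on them removes whatever part of the therapy effect runs through them, and can add confounding if an unmeasured factor affects both marker and MADRS.

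The risk is that a coefficient from this extended model is read as the effect of GMT or RCS on depression in the substudy.

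**Working it through.** **Inputs (Sections 2.2, 2.7 and 2.9).** 50 residents in each of four arms; 20% dropout by 6 months; average cluster size 8 after dropout; ICC at most 0.01 for the biological indicators; two-sided 2.5% level; 80% power; stated detectable d = 0.51. No saliva in one of the four arms.

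**1. The plan's own figure.** Residents at 6 months: 200 × 0.8 = 160, or 80 vs 80 for each factorial contrast. Design effect: 1 + (8 − 1) × 0.01 = 1.07. Effective size per side: 80 / 1.07 = 74.8. Normal approximation: d = (2.241 + 0.842) × √(2 / 74.8) = 0.504. With the noncentral t distribution d = 0.509, and power at d = 0.51 is 80.2%. The stated 0.51 reproduces.

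**2. Residents lost.** The combined arm is 50 of 200 at baseline and 50 × 0.8 = 40 of 160 at 6 months, which is 25%. At most 160 − 40 = 120 remain. The further saliva exclusions make 25% a minimum.

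**3. Precision, for illustration, same method at ICC 0.01.** With one factor in the model, GMT is compared with RCS and control together (40 vs 80). With both factors in, each coefficient is one music arm against control (40 vs 40).

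| Comparison | Effective sizes | Detectable d | Power at d = 0.51 |
|---|---|---|---|
| Four arms, 80 vs 80 | 74.8 vs 74.8 | 0.51 | 80% |
| Three arms, 40 vs 80 | 37.4 vs 74.8 | 0.62 | 61% |
| Three arms, 40 vs 40 | 37.4 vs 37.4 | 0.73 | 47% |

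This ICC is stated for biological indicators. Section 2.9 expects the cluster effect to be larger for MADRS but gives no value. Assuming 0.05 to 0.10 (design effects 1.35 to 1.70), the detectable d goes from 0.57–0.64 in four arms to 0.70–0.79 (40 vs 80) or 0.82–0.92 (40 vs 40).

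**4. Direction of the shift in the therapy coefficient (all values assumed).** Let therapy move the marker by a = 0.3 SD, let the marker have slope b = 0.3 on MADRS, and let the direct effect be c = 0.40.

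- Total effect: c + a × b = 0.40 + 0.09 = 0.49.
- Coefficient after adjusting for the marker: 0.40.
- If an unmeasured factor loads 0.5 on both marker and MADRS, the fitted marker slope is 0.3 + 0.25 / 1.25 = 0.50, and the adjusted coefficient is 0.49 − 0.3 × 0.50 = 0.34.
- If a = 0, the coefficient does not move.

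The article supplies none of a, b or c, so this shows the mechanism and not a predicted size.

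**The case against.** The strongest reply is that nothing in the article says the extended model supplies the therapy effect. Section 2.10.2 can be read as a sequence of models, and comparing the therapy coefficient before and after adding a candidate mediator is a familiar, if imperfect, way to approach mechanism. It would fit the abstract's promise: "Insights into mediatory effects of stress to explain the effect of music interventions will be gained". Section 2.11 restates the MADRS model without the saliva terms. On this view the fault is one ambiguous sentence in a secondary analysis of an exploratory substudy. That limits the severity, but it does not rescue the sentence: as a mediation step it would still need to be labelled as such and confined to three arms, and Section 2.10.2 does neither.

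Several stronger readings are tempting, and the documents do not support them:

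- **That the substudy's main results are biased.** The co-primary hair cortisol and PSS-10 models (Section 2.10.1) use all four arms and contain no saliva term, and the MADRS model without the added terms is intact.
- **That the time points of the correlations contradict each other.** Section 2.10.2 correlates saliva responses at T3 and T6 with MADRS change. The Section 2.11 sentence, "The analyses included a correlation between stress reduction (at T3, pre-post treatment) and change in MADRS score", closes the paragraph on hair cortisol and PSS-10 and may be a different analysis.
- **That these correlations are pooled over arms.** The article is silent, and such detail is commonly left to a fuller document. The same holds for a fully specified mediation model.
- **That the article claims baseline saliva.** The mention of baseline describes the design as a whole, which has T0 values for hair cortisol, PSS-10 and MADRS.

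**Conclusion.** The concern holds for the one sentence in Section 2.10.2. Followed as written, it costs at least 25% of the expected substudy sample (40 of 160) under complete-case fitting. It leaves the additional GMT + RCS effect inestimable. It also yields a therapy coefficient that is not the total effect to the extent that therapy changes the markers, as Section 2.6.3 hypothesises for salivary cortisol. The first two consequences follow from the design; the size of the third cannot be derived from the article. The rise in detectable d from 0.51 to 0.62 or 0.73 is illustrative, because it borrows the biological ICC, and the loss for MADRS would be greater.

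That the session VAS is also absent in the combined arm is inferred from its link to saliva days and from that arm's restriction to the longer-term question in Section 2.7. The mismatch between three and four groups is a real inconsistency. Severity is moderate: the model is secondary and exploratory, and the co-primary analyses are untouched.

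**What to change.** 1. Delete the sentence in Section 2.10.2. Take the MADRS therapy effect from the four-arm model with baseline covariates only, which agrees with Section 2.11.
2. Analyse salivary cortisol, α-amylase and the VAS as outcomes in the three arms that have them: post-session minus pre-session change, each music arm against book reading.
3. If these markers are to be studied as mediators, do so in a separate three-arm model labelled exploratory, with the caveat that it assumes no unmeasured confounding. Alternatively, use hair cortisol at T3 with MADRS at T6, which keeps all four arms and the right time order.
4. Adjust any saliva–MADRS association for arm, as a precaution.
5. Reconcile the three groups of Section 2.10.2 with the four groups in the saliva paragraph of Section 2.11.

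The cost is wording, plus one further model on data already planned if mediation is pursued. No new assessments are needed.
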